#### Trial-specific preventive measures

There are no specific restrictions associated with ASA/placebo medication. All of the patients included in the study are already under ASA treatment beforehand, therefore no restrictions apply.

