## Methods

### Aim

The aim of this study is to undertake a randomized controlled trial on the recurrence and cardiovascular complication rates of patients undergoing burr-hole drainage of cSDH with and without discontinuation of low-dose ASA in the perioperative phase.

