### Statistical consideration

#### Number of participants with rationale

A systematic review by Almenawer et al. [23] reported an overall recurrence rate of approximately 10.7% for cSDH in the normal population. According to the literature, recurrence rates in the normal population range from 5% to 30% [24]. Recurrence rates have been described to reach 33% under antithrombotic therapy with ASA [12, 14]. In a retrospective study we conducted in patients where ASA treatment was continued, a recurrence rate of 22% was observed [15]. Based on the available data from the literature, we hypothesized that the recurrence rates after burr-hole drainage of cSDH under ASA treatment (π_ASA_) and without ASA treatment (under placebo, π_Placebo_) are 28% and 10%, respectively. The sample size was set to ensure at least 80% power (1 – β = 0.8), at a significance level of α = 5%. The sample size was estimated using a resampling procedure in which different sample sizes were each evaluated 999 times by drawing random samples of events based on these assumptions. This indicated that randomizing 142 patients should allow us to show the assumed difference in event rates between the groups.

The primary analysis will be performed on the full analysis set – consisting of all patients who are randomized to the study, regardless of protocol violations – and based on the intention to treat principle. The primary analysis is a comparison of incidence rate. The difference in incidence rate will be tested and a 95% confidence interval for the difference constructed. In case of many losses to follow-up, inverse probability censoring weights will be used to deal with missing outcome data. A sensitivity analysis will be performed on the per protocol analysis set. In the primary analyses, the type-I error rate for significance will be taken as α = 0.05. As secondary analysis, a time-to-event analysis will be performed comparing the hazard of recurrence between treatment arms using a Cox proportional hazards model. Secondary outcomes will be analyzed using generalized linear regression models with appropriate distribution family, depending on the outcome (binomial for binary outcome, Poisson for counts, Gaussian for continuous, normally distributed, outcomes).

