#### Compliance with study intervention

During hospitalization, compliance will be monitored by study nurses. After hospital discharge, patients will be instructed to continue taking medication until the 12th postoperative day. Compliance during the ambulatory phase of the trial will be controlled by patient or caregiver interviews during the clinical follow-up after 6 weeks. The patients will be explicitly asked if they took the study medication up to the 12th postoperative day and the empty blister and the rest of the medication, if there is one, will be collected. In case of non-compliance, a note-to-file will be completed and taken into account in the final statistical evaluation.

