#### Concomitant interventions (treatments)

Not applicable.

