#### Primary analysis

The difference in recurrence rate (π_Asp_–π_placebo_) will be tested by calculating a two-sided 95% confidence interval of the difference in proportions. Inverse probability censoring weights will be used to prevent selection bias in case of many losses to follow-up. The analysis will be performed primarily on the FAS. Sensitivity analyses will be performed on the per protocol set.

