### Limitations

Although this is a randomized, double-blinded, placebo-controlled study, it has some limitations. Since burr-hole drainage is preformed either as an emergency or elective procedure, pre- and postoperative discontinuation time of ASA differs between the patients. By assuring that all patients under placebo will discontinue ASA at least 7 days after surgery, this bias should be minimal. Patients are often discharged before the study medication is sustained, and therefore compliance of the intake cannot be guaranteed in all patients. In order to minimize this bias, we will collect the empty medication boxes at the first follow-up visit. We expect the study to be multicentric by the first quartal of 2019, which will definitely lead to an improvement in the study quality.

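### The compliance check as described cannot verify that placebo patients stayed off their own ASA, and the sections on restrictions and concomitant treatment do not fit the sections that rely on this

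*Protocol article*

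**What the plan says.** The Aim section sets the comparison as burr-hole drainage "with and without discontinuation of low-dose ASA in the perioperative phase". Placebo is therefore the discontinuation arm. The Limitations section leans on this: "By assuring that all patients under placebo will discontinue ASA at least 7 days after surgery, this bias should be minimal".

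The sections that bear on whether this is achieved are:

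- **Trial-specific preventive measures:** "There are no specific restrictions associated with ASA/placebo medication". The reason given is that all participants were on ASA before the study.
- **Concomitant interventions (treatments):** "Not applicable".
- **Compliance with study intervention:** study nurses monitor compliance in hospital. After discharge there is a patient or caregiver interview at about 6 weeks: "The patients will be explicitly asked if they took the study medication up to the 12th postoperative day". Used blisters and leftover study medication are collected.
- **Limitations:** patients frequently go home before the course is finished, and intake then cannot be guaranteed. The remedy named is collecting the empty boxes.
- **Unblinding procedures:** after a thrombotic event ASA is restarted in either arm.
- **Datasets to be analyzed:** patients who received the treatment opposite to their allocation leave the per-protocol set.

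**The concern.** Every participant is a current or former user of the same product that serves as study drug. The behaviour that matters for the control arm is therefore ASA taken outside the blister, as well as study tablets missed. The described check looks only at the second.

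If ASA acts as the sample size section assumes, unrecorded use in the placebo arm moves the observed recurrence difference toward zero. It would also reduce any excess of thrombotic events caused by stopping ASA, which is the trial's other question. The per-protocol analysis is the planned sensitivity analysis, but its crossover exclusion can act only on crossover that someone has written down. If use goes unrecorded, both analyses carry the same dilution and their agreement reassures falsely. The information cannot be recovered reliably once the trial is over.

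**Working it through.** **1. Can the described check detect own-supply ASA?** Take a placebo patient who swallows every study tablet and also takes ASA from a personal supply.

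| Check | Where described | Result for this patient |
|---|---|---|
| Interview at about 6 weeks on study medication | Compliance with study intervention | Truthful yes |
| Return of blisters and leftovers | Compliance with study intervention | Empty, as expected |
| Return of empty boxes | Limitations | Empty, as expected |
| Postoperative visit lists (days 1, 2, 7 or discharge, 4–6 weeks, 6 months) | Study measurements | No item on non-study ASA |
| Crossover exclusion | Datasets to be analyzed | Not triggered, because nothing is recorded |

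Other antithrombotics are listed only at admission, under patient characteristics. The schedule figure was not available for this check.

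**2. Where is the gap open?** Nurse monitoring covers the hospital stay. That leaves the days after discharge and, for elective patients randomized 5 days before surgery, any preoperative days spent at home.

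**3. Do the sections agree with each other?**

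- The concomitant-treatment entry conflicts with three others. Unblinding procedures has ASA restarted after a thrombotic event, Secondary analyses plans sub-analyses of patients on clopidogrel or oral anticoagulants, and the missing-data section plans one for concomitant blood thinners.
- The preventive-measures section assumes that all patients are already on ASA. The inclusion criteria also admit users whose ASA had been stopped.
- The period differs. Drug used gives 12 days from randomization, the compliance section runs to postoperative day 12, and Limitations refers to at least 7 days after surgery. For an elective patient, 12 − 5 = 7, so the first period ends at about postoperative day 7 and the second runs 5 days longer. The text does not settle what applies to own ASA in that interval.

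**4. How much could it matter?** Inputs from the sample size, randomization and primary analysis sections: 28% on ASA, 10% on placebo, 142 patients at 1:1 (71 per arm), "The sample size was set to ensure at least 80% power", α = 5%, and a "two-sided 95% confidence interval of the difference in proportions".

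First, the plan's own figure, with unpooled variance:

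n = [0.28 × 0.72 + 0.10 × 0.90] × (1.960 + 0.842)² / 0.18² = 0.2916 × 7.849 / 0.0324 = 70.6, so 71 per arm and 142 in total.

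This matches. Full enumeration of the two binomials at 71 per arm, with the Wald interval excluding zero, gives 80.2% power.

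Now let a share f of placebo patients cross over, each carrying the ASA-arm risk: placebo rate = 0.10 + 0.18f. The documents give no value for f, so the range is assumed.

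| f | Placebo rate | Difference (points) | Power, enumerated |
|---|---|---|---|
| 0 | 10.0% | 18.0 | 80.2% |
| 5% | 10.9% | 17.1 | 75.0% |
| 10% | 11.8% | 16.2 | 69.4% |
| 20% | 13.6% | 14.4 | 57.4% |

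The pooled-variance formula gives 78.7%, 73.5%, 68.0% and 56.2% for the same rows, so the pattern does not depend on the choice of test.

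**The case against.** The strongest reply is that the rule exists and only its verification is unstated. The Limitations section says placebo patients stop ASA. Restarting ASA after a thrombotic event makes sense only if own ASA is otherwise stopped. Nurses watch compliance in hospital, data are checked for protocol violations, and recorded non-compliance feeds into the evaluation. This stands. A reader might infer that nothing stops patients taking their own ASA, or that the protocol permits it; the documents do not support that.

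The preventive-measures statement can also be read as saying that the study drug needs no special precautions in people who already take it. That reading is fair, and on it the section is silent about own ASA. The ambiguity still needs removing, because this is the only section on restrictions.

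A third reply is that interview wording and medication pages belong to the full protocol, so one cannot say that own ASA will go unmeasured. That is right, and the claim here is narrower: the check that the article does set out, followed exactly, cannot confirm the assurance that the article itself relies on.

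Finally, the crossover share is hypothetical, and giving each crossover patient the full 28% risk is toward the severe end. A few days of use after discharge would be expected to dilute less. This also stands, and the figures are labelled accordingly. Doubled dosing in the ASA arm could be raised as well, but the documents give nothing on its frequency, and it is a clinical question left aside here.

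**Conclusion.** The point holds as a gap in verification together with sections that do not fit each other. Placebo patients are meant to be off ASA, but the stated checks would pass one who was not, and that patient would count as having discontinued in both the full and per-protocol analyses. The entry on concomitant treatment contradicts three other sections, and the study-drug periods disagree.

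The size is unknown. The loss from 80% power to between 75% and 57% rests on an assumed crossover of 5% to 20%, on full ASA risk in those patients, and on the plan's own event rates. It is an illustration, not a forecast. A reader might infer that 142 is too small; that does not follow, since the figure reproduces exactly under its stated assumptions. It simply carries no stated allowance for crossover. This is a worthwhile, inexpensive improvement and not a fault that undermines the design.

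**What to change.** 1. Reconcile Trial-specific preventive measures and Concomitant interventions with Unblinding procedures, Secondary analyses, Handling of missing data and Limitations, so that the handling of the patient's own ASA is stated once for both arms. The clinical rule is for the sponsor to set.
2. Reconcile the study-drug periods in Drug used, Compliance with study intervention and Limitations.
3. Extend the nurse check and the 6-week interview to record, with dates, any ASA or other antiplatelet taken outside the study blister from randomization to the last study dose, including the preoperative days of elective patients.
4. State under Datasets to be analyzed that recorded own-supply ASA in the placebo arm during that period counts as receiving the opposite treatment for the per-protocol set. Record ASA restarted after a thrombotic event separately, with its reason, and say how it counts.
5. Report the proportion with non-study ASA by arm.

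The cost is protocol wording and one extra CRF item at contacts that already take place. The answers depend on recall at about 6 weeks, and the per-protocol set becomes slightly smaller. The full-analysis estimate does not change, but a reader can then judge how far the placebo arm really discontinued.

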**Methods:**

In this prospective randomized, placebo-controlled, double-blinded study we include all patients undergoing burr-hole drainage of cSDH who are under ASA treatment. The patients are randomized into two groups, one receiving ASA and the other placebo perioperatively. The study primarily seeks to compare the rate of recurrent events under ASA to that under placebo treatment. Secondary objectives are thromboembolic event rate, perioperative blood loss, postoperative anemia, intra- and postoperative blood transfusion rate, and clinical outcome.

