### Inclusion criteria

Informed consent as documented by signaturePatients undergoing burr-hole drainage for cSDH who are under low-dose ASA treatment (Aspirin cardio^®^ 100 mg once a day)ASA users under discontinued ASA treatment (e.g., conservatively managed for a period of time and ASA was discontinued)Patients older than 18 years

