### Drug used

Aspirin cardio® (ASA), 100 mg 1–0-0/d, administered for 12 days after randomization.

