### Study measurements

#### Preoperatively/at admission

Cranial computed tomography (cCT): midline shift (MLS), hematoma width, hematoma characteristics (laminar/trabecular/septated/homogenous)Patient characteristics (age, medical history, oral anticoagulants/Clopidogrel/novel oral anticoagulants, history of falls, history of burr-hole drainage)Neurologic evaluation (NE), Glasgow Coma Scale (GCS), mRS, GOS, Markwalder score12-channel electrocardiogram (ECG)Blood pressure (BP), saturation (SAT), heart rate (HR)Laboratory tests (hemoglobin, thrombocytes, quick, international normalized ratio (INR), platelet function assay bleeding time, troponin)

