#### Randomization

Each eligible patient will be allocated to ASA or placebo group either on the first postoperative day (in case of emergency operation on the same day), or preoperatively (in case of emergency operation 24 h after last ASA intake, or in case of elective surgery 5 days before operation).

Randomization will be performed by an independent individual using an unstratified block randomization procedure as implemented in the electronic data capture software SecuTrial. An allocation ratio of 1:1 and a block size of 8 will ensure a balance in sample size across both groups over time.

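### The protocol says every patient is already on ASA, yet it admits patients whose ASA has been stopped; for them the trial tests resuming ASA, not continuing it

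*Protocol article*

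**What the plan says.** All places are in the protocol article.

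- **Trial-specific preventive measures:** "All of the patients included in the study are already under ASA treatment beforehand, therefore no restrictions apply".
- **Abstract, Methods:** the same population is described, "we include all patients undergoing burr-hole drainage of cSDH who are under ASA treatment".
- **Inclusion criteria:** after current low-dose ASA users, a separate criterion admits "ASA users under discontinued ASA treatment (e.g., conservatively managed for a period of time and ASA was discontinued"). It sets no limit on time since the last dose.
- **Aim:** recurrence and cardiovascular complications are to be compared "with and without discontinuation of low-dose ASA in the perioperative phase".
- **Drug used:** in the active arm ASA is "administered for 12 days after randomization", with no distinction by ASA status at entry.
- **Randomization (under Statistical consideration):** allocation is made "using an unstratified block randomization procedure as implemented in the electronic data capture software SecuTrial".
- **Statistical analysis:** the primary analysis covers all randomized patients. The named subgroups are sex and concomitant blood thinners.
- **Limitations:** differing discontinuation times are acknowledged, but are put down to emergency versus elective surgery. Patients who enter with ASA already stopped are not mentioned.

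**The concern.** Two statements in the current text cannot both be true. The first carries weight, because it is the only reason given for having no restrictions with the study medication. For an explicitly eligible group, that reason does not apply.

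The second consequence is for the question asked. A patient on ASA at presentation is randomized between keeping the drug and losing it. A patient already off ASA is randomized between getting it back and remaining without it. Both are legitimate contrasts, but only the first matches the stated aim. Pooling them gives a weighted average whose weights are the unknown shares of the two kinds of patient. If the effect differs between them, a conclusion worded as continuing versus discontinuing ASA describes neither group exactly.

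**Working it through.** **1. The sections side by side.**

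| Section | ASA status at entry |
|---|---|
| Trial-specific preventive measures | all already on ASA |
| Abstract, Methods | on ASA |
| Inclusion criteria | on ASA, or ASA already discontinued |
| Aim | presupposes ASA that can be discontinued |

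Reading the word for *beforehand* loosely, as at some earlier time, does not rescue the first row. That sentence places patients under treatment, while the inclusion criterion describes treatment that has been stopped.

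**2. The contrast by entry status** (from Inclusion criteria and Drug used).

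| Status at entry | ASA arm | Placebo arm | Matches the aim? |
|---|---|---|---|
| On ASA | continues | discontinues | yes |
| Already off ASA | resumes | stays off | no |

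In both rows ASA versus placebo is randomized, so neither row is biased.

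**3. The plan's own figure.** Inputs from Number of participants with rationale: 28% versus 10%, 80% power, α = 5%, 142 patients. The test is the two-sided 95% interval for a difference in proportions (Primary analysis).

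n per arm = (1.96 + 0.8416)² × (0.28 × 0.72 + 0.10 × 0.90) / 0.18² = 70.6, so 71 per arm and 142 in total. This reproduces. Exact enumeration of the Wald interval test at 71 per arm gives 80.2% power.

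**4. Sensitivity of power (illustration only).** Let s be the share already off ASA and f the effect in them as a fraction of 18 points. The document gives neither. With placebo at 10% and 71 per arm:

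overall difference = 0.18 × [(1 − s) + s × f]

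| s | f | Difference (points) | Exact power |
|---|---|---|---|
| any | 1 | 18.0 | 80.2% |
| 20% | 0.5 | 16.2 | 72.7% |
| 40% | 0.5 | 14.4 | 63.8% |
| 20% | 0 | 14.4 | 63.8% |
| 40% | 0 | 10.8 | 43.4% |
| 20% | 1.25 | 18.9 | 83.4% |
| 40% | 1.25 | 19.8 | 86.2% |

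A share of only 10% with half the effect gives 76.7%.

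Values of f above 1 are not fanciful. Patients having a same-day emergency operation are randomized on the first postoperative day, so current users in either arm may be operated on with recent ASA exposure. Placebo patients who stopped earlier have been off the drug longer, so the contrast in the stopped group could be the larger one.

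**5. What a result by status could show.** Expected events: 71 × 0.28 + 71 × 0.10 = 19.9 + 7.1 = 27.0. At the full planned effect, a 20% subgroup (about 28 patients) would hold 0.2 × 27.0 = 5.4 events, and a 40% subgroup (about 57 patients) 10.8. The half-width of a 95% interval for the risk difference is 1.96 × √[(0.28 × 0.72 + 0.10 × 0.90)/m], with m patients per arm. It is 28 points at m = 14.2 and 20 points at m = 28.4.

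**The case against.** The strongest reply is that the randomized question is coherent. The abstract frames the primary comparison as recurrence under ASA against recurrence under placebo, and every entrant is an ASA user allocated to one or the other around surgery. Admitting users whose ASA was recently stopped is a pragmatic choice, and the limitations section partly discloses the varying time off drug. This stands as far as it goes: there is no allocation bias. It does not remove the contradiction about who is enrolled, and the disclosed reason is a different one.

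Three stronger readings are tempting, and the document does not support them.

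- **That the 28% versus 10% comes from continued-ASA data.** Only the 22% from the sponsor's retrospective study is tied to continued ASA. The 33% is described as recurrence under antithrombotic therapy with ASA, and the lower figures refer to the normal population. The hypothesis itself is worded as with and without ASA treatment, which fits stopped users too.
- **That the two groups cannot be separated in the data.** The admission list names "oral anticoagulants/Clopidogrel/novel oral anticoagulants, history of falls, history of burr-hole drainage" and does not itemize ASA status. But it is a condensed list that includes medical history. One randomization route depends on the time of last ASA intake, and discontinued ASA is itself an entry criterion, so status is probably known at screening. What can be said is that no listed baseline item or analysis distinguishes the groups.
- **That the trial is underpowered for this reason.** The table shows that the answer depends entirely on assumed values.

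It is also fair to say that covariates and further subgroups often sit in an analysis plan, which is not shown, and that an interaction test on about 27 events would be weak. The first is why the point rests on the contradiction and the aim rather than on a missing subgroup. The second is why the result by status should be labelled exploratory.

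**Conclusion.** The point holds as a contradiction about the enrolled population and a mismatch between eligibility and aim. The stated basis for having no restrictions is untrue for an explicitly eligible group, and for that group the trial compares resuming ASA with staying off it.

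This concerns the population and the wording of the conclusion, not the validity of the randomized comparison. A reader might infer a demonstrated loss of power. The document supports neither its size nor its direction: for shares of 20% to 40%, power ranges from 43% (no effect in stopped users) through 80.2% (equal effect) to 86% (an effect 1.25 times as large). These shares and effects are assumptions. The textual conclusion depends on none of them.

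**What to change.** - Reconcile the abstract, the aim, the inclusion criteria and Trial-specific preventive measures, including the stated reason for having no restrictions. Which clinical rule should apply is for the investigators; none is proposed here.
- Record at randomization whether ASA is current or already discontinued, and the date of last intake.
- Pre-specify an analysis of the primary endpoint adjusted for that status. Report the risk difference by status with an interaction estimate, labelled exploratory.
- Word any conclusion about continuing ASA for patients who were on it at presentation.

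The cost is two baseline fields and one additional analysis. The downside is imprecision: with about 27 events in all, the subgroup intervals will be wide, and a non-significant interaction must not be read as evidence that the two groups respond alike.
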